### Data collection

An overview of the data collection strategies is shown in Table 3. Four types of quantitative data are collected: drug-related problems and interventions, medication refill records, patient questionnaires and descriptive pharmacist information. If patients would withdraw consent, no additional data is registered but existing data is preserved.

**Table 3 Tab3:** Overview of the data collected for the SIMENON study

Data collection	A. Drug-related problems & interventions	B. Adherence	C. Questionnaires	D. Descriptive pharmacist information
Subject	Patient	Patient	Patient	Pharmacist
Collector	Pharmacist	Pharmacist	Researcher	Pharmacist
Sample size	900 patients	900 patients	140 patients	75 pharmacies
Method	Questionnaire: webtool	Medication refill records	Questionnaire: by letter, by phone or by e-mail	Questionnaire
Frequency	Four times	Once	Three times	Once
Timeframe	During the medication review process	• 9 months before • 9 months after the review	• 1 week before the review • 3 weeks after the review • 12 weeks after the review	Before start of the study
Content	• Administrative and medical data • DRPs and interventions • Duration • GP contacts	Medication refill records	• Adherence • Self-management • Polypharmacy burden • Satisfaction • Demographic data • Use of emergency healthcare services • Fall incidents	• Pharmacy and Pharmacist characteristics • Pharmacist experiences

For each patient receiving a review, an online registration form is completed by the pharmacist via a webtool (available upon request). Pharmacists are required to login to use this webtool and only coded patient information can be registered. Drug-related problems and interventions are registered throughout the medication review process using the PharmDISC classification system [18]. Permission was given by the authors to translate and use the instrument. Participating pharmacists are given a manual with explanation and examples to ensure the quality of the classification. Medication refill data is collected of all participants in the study to estimate adherence before and after the medication review. Data is collected from 9 months before until 9 months after the review. Finally, all participating pharmacists are required to fill in a questionnaire related to pharmacy and pharmacist characteristics.

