### Data analysis

First, descriptive statistics will be used to characterize the study population using demographic parameters, to give an overview of drug-related problems, interventions and level of implementation. Secondly, adherence will be calculated using two methods for the analysis of refill data: the medication possession ratio as well as proportion of days covered. The impact will be measured by comparing data before and after the intervention using appropriate statistical tests for paired data. Subsequently the correlation between objective measures for adherence (medication refill records) and subjective measures (PROMAS score) will be investigated [21]). In addition, the results of these adherence measures will be compared with the registered drug-related problems and interventions. This provides insight in the number of (un)detected adherence problems and the effectiveness of a medication review and interventions to improve adherence.

Third, patient questionnaires will be scored in accordance with the described methods of the original authors. The impact of the intervention will be explored using appropriate statistical tests for paired data. Subgroup analysis will compare the baseline scores in the three types of data collection (letter, phone or email) to ensure the quality of the data.

A final analysis aims to identify patients with a high risk of drug-related problems by investigating the impact of variables on the number of drug-related problems detected by pharmacists. These variables have been defined a priori based on scientific research as well as patient criteria for a medication review in countries abroad. Both patient related factors, process factors and pharmacy related factors will be explored. All analysis will be performed using the statistical program SPSS. A per protocol analysis and a listwise deletion will be applied.

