### Sample size

The study aims to approach 75 pharmacies in Belgium, approximately half in Flanders and half in Wallonia. Each pharmacy in turn includes 12 patients. This brings the total number of participants to 900 (Table 5). The primary aim of this study is to describe the type and number of drug-related problems and related interventions for each patient. In this way, the primary outcome is a process measure. The secondary outcome is medication adherence. A systematic review by Hatah et al. shows that both an intermediate and advanced medication review by community pharmacists significantly improves adherence [7]. Provided that the pharmacist can improve adherence using a medication review in half of the patients with a low adherence (10% of all older patients) and a significance level of 5% and power of 80%, a sample size of 746 patients is calculated [21, 22]. Taking into account a drop-out rate and missing data (17%, *n* = 154) a sample size of 900 participants is proposed.

**Table 5 Tab5:** Sample size

Sample size	Medication review	Questionnaires
Number of Belgian community pharmacies	75	35
Number of participating patients per pharmacy	12	4
Total number of participating patients	900	140

For the patient reported outcomes using questionnaires, all Dutch-speaking patients in the Flemish community pharmacies (approximately 35) are approached. It is hypothesized that 2/3 of patients who consent to a medication review also agree to complete the questionnaires. Considering a drop-out rate of 50%, data should be available for 140 patients (Table 5). In this subset, the score on the Living with Medicines Questionnaire is the main outcome. However, since this instrument has not yet been used in an older polymedicated population, no sample size calculation can be performed.

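### Per protocol with listwise deletion is the only analysis rule stated, yet half the questionnaire patients are expected to drop out, so the before-after LMQ change is estimated in completers only

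*Protocol article*

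**What the plan says.** The study is a single-group pretest-posttest design (protocol article, Design, setting and study period). For the questionnaires, the Data analysis section states: "The impact of the intervention will be explored using appropriate statistical tests for paired data". The section ends with the rule for the analysis set and missing values: "A per protocol analysis and a listwise deletion will be applied". It names no wider analysis set, no model for incomplete data, no sensitivity analysis and no comparison of completers with drop-outs. The one questionnaire subgroup comparison is of baseline scores by mode of collection.

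The Sample size section sets out the questionnaire subset: "all Dutch-speaking patients in the Flemish community pharmacies (approximately 35) are approached"; "Each pharmacy in turn includes 12 patients"; "It is hypothesized that 2/3 of patients who consent to a medication review also agree to complete the questionnaires". It then states: "Considering a drop-out rate of 50%, data should be available for 140 patients (Table 5"). On the endpoint it says: "In this subset, the score on the Living with Medicines Questionnaire is the main outcome". LMQ is collected at T-1w, T3w and T12w (Table 4).

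For patients who withdraw consent, the Data collection section says that "no additional data is registered but existing data is preserved".

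**The concern.** A paired test restricted to complete cases estimates the change in patients who stayed. In a randomised comparison, some of the resulting distortion may be shared by both arms. Here there is no second arm, so any link between staying in and the score goes straight into the estimated effect. The plan itself expects to lose half of those who start the questionnaires, and these questionnaires are how it evaluates effectiveness from the patient's side.

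The Discussion acknowledges selection at entry, in that motivated patients are more likely to join, but does not mention selection through drop-out. The protocol uses fixed inclusion days to limit selection bias at recruitment, and a completer-only analysis can bring selection back later.

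Two further losses depend on how the rule is read. If listwise deletion runs across all visits, a patient with LMQ at T-1w and T3w but not T12w contributes nothing, even to the three-week comparison. If per protocol means completing steps 5 and 6 of the review, drug-related problems and refill records already held for other patients are left out needlessly, because neither depends on those steps.

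**Working it through.** **Reproducing the plan's figure.** Inputs from the Sample size section: 35 pharmacies, 12 patients each, 2/3 agreeing to questionnaires, 50% drop-out.
- Review patients: 35 × 12 = 420.
- Start the questionnaires: 420 × 2/3 = 280.
- Remain: 280 × 0.5 = 140, which agrees with Table 5 (35 × 4 = 140).

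The analysed patients are half of those who start and one third of the 420.

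**Detectable change with 140 pairs.** A paired t-test at two-sided 5% and 80% power detects 0.238 SD of the change score. With correlation r between visits, the SD of change is √(2(1 − r)) baseline SD.
- r = 0.6: √0.8 = 0.894, so 0.238 × 0.894 = 0.21 baseline SD.
- r = 0.7: √0.6 = 0.775, so 0.238 × 0.775 = 0.18 baseline SD.

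**Bias when the true change is zero.** The documents give no drop-out mechanism, so these inputs are assumptions: normal scores with SD 1 at each visit, overall completion 50%, and a logistic probability of completion with slope 0.5 to 1.0 per baseline SD. Results are from simulation with 2 million patients.

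*Loss depends on baseline score.* The false change is (1 − r) times the shift in completers' mean baseline score. That shift is about 0.235 SD at slope 0.5 and 0.413 SD at slope 1.0.
- r = 0.6: 0.4 × 0.235 = 0.09; 0.4 × 0.413 = 0.17.
- r = 0.7: 0.3 × 0.235 = 0.07; 0.3 × 0.413 = 0.12.

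If patients with high scores leave, the false change is positive (regression to the mean). If patients with low scores leave, it is negative.

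*Loss depends on the change from T-1w to T3w.* If patients whose score rises are the ones who leave, the false change at T12w is:

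| Correlations | Slope 0.5 | Slope 1.0 |
|---|---|---|
| 0.7 between T3w and T12w, 0.6 otherwise | −0.12 | −0.21 |
| all 0.6 | −0.10 | −0.17 |
| all 0.7 | −0.07 | −0.13 |

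The signs reverse if patients whose score falls are the ones who leave.

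*No dependence.* If drop-out is unrelated to score or change, the bias is zero.

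**Does the alternative help?** In the same simulations, T12w was predicted from T-1w and T3w, with the relation estimated in completers and applied to all starters. The estimated change was 0.00 under every mechanism above. This assumes that the starters who drop out have both earlier scores and that loss depends only on those scores.

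**Cross-check by a different route.** In a normal selection model with 50% retained, the bias in SD of change is ρ × 0.399/0.5, where ρ is the correlation between staying in and change. For ρ = 0.1, 0.2 and 0.3 this gives 0.08, 0.16 and 0.24, against a detectable 0.24 on the same scale.

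**The case against.** The strongest reply is that the rule is short and undefined, and that too much can be read into it. Several stronger readings are tempting, and the documents do not support them.

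- *That per protocol excludes patients without steps 5 and 6 from the drug-related problem and refill analyses.* The article calls the follow-up consultation obligatory, so this is a natural reading, but per protocol is nowhere defined.
- *That T-1w and T3w values are certainly thrown away.* The article does not say whether listwise deletion applies to each comparison or across all visits. The sentence on preserving data concerns withdrawal of consent only and does not say that the data go unused.
- *That the study's main result is biased.* The main outcome is a description of the type and number of drug-related problems, not a before-after change, and no bias in it has been shown. The 17% allowance for refill data (154 of 900) combines drop-out with missing data. A new analysis set cannot recover records that do not exist.
- *That completers are self-selected in a known direction.* Reasons for drop-out are not given. The two mechanisms above can have opposite signs and could partly cancel, and only the steepest slope reaches the detectable effect.

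The reply is also right that LMQ is the third outcome, that its change is to be explored without a sample-size calculation, and that the Discussion concedes the lack of a control group and limited generalisability. These points limit the reach and severity of the concern. They do not answer it: a completer-only paired analysis, with half the starters expected to be missing and no check on that loss, is a stated choice and not a detail left to another document.

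**Conclusion.** The concern holds for the questionnaire outcomes, and chiefly for LMQ. The plan estimates change in about 140 of 280 starters, in a single group, with no analysis that uses the incomplete cases or examines them. Under the assumed mechanisms the bias is about 0.07 to 0.21 baseline SD in either direction, so at its upper end it equals the change that 140 pairs can detect. Under drop-out unrelated to score or change it is zero. The documents do not show which applies.

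The loss of T-1w and T3w values, and of drug-related problem and refill data, is conditional on readings that the article leaves open. That ambiguity is itself a reason to rewrite the sentence. A reader might infer that every analysis in the study is compromised, but the documents support only the narrower point. This is a should-fix.

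**What to change.** Replace the closing sentence of the Data analysis section with the following.

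1. **Questionnaires.** Analyse LMQ with a likelihood-based mixed model for repeated measures, with T-1w, T3w and T12w as a factor, including every patient with at least one assessment. For outcomes measured only at T-1w and T12w, use all available data with a model suited to the outcome type, for example a binary or count model for falls and emergency care.
2. **Drug-related problems and refill adherence.** Describe drug-related problems in all patients with a T0 interview. Analyse refill adherence in all patients with available refill records. Do both whether or not steps 5 and 6 were completed, and respect the rule that nothing further is registered after consent is withdrawn.
3. **Sensitivity and transparency.** Keep the per protocol, listwise analysis as a sensitivity analysis, with both terms defined. Tabulate completers against drop-outs at baseline.

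The cost is a rewritten paragraph and some extra analysis; none of these steps needs new data, and SPSS, already named, fits mixed models. The model relies on data being missing at random. It does not correct loss that depends on unobserved values, it gains little on change from patients with baseline only, and it cannot include patients who return no questionnaire. The table of completers against drop-outs is therefore needed as well. The estimated effect may move in either direction.

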### Sample size

The study aims to approach 75 pharmacies in Belgium, approximately half in Flanders and half in Wallonia. Each pharmacy in turn includes 12 patients. This brings the total number of participants to 900 (Table 5). The primary aim of this study is to describe the type and number of drug-related problems and related interventions for each patient. In this way, the primary outcome is a process measure. The secondary outcome is medication adherence. A systematic review by Hatah et al. shows that both an intermediate and advanced medication review by community pharmacists significantly improves adherence [7]. Provided that the pharmacist can improve adherence using a medication review in half of the patients with a low adherence (10% of all older patients) and a significance level of 5% and power of 80%, a sample size of 746 patients is calculated [21, 22]. Taking into account a drop-out rate and missing data (17%, *n* = 154) a sample size of 900 participants is proposed.

**Table 5 Tab5:** Sample size

Sample size	Medication review	Questionnaires
Number of Belgian community pharmacies	75	35
Number of participating patients per pharmacy	12	4
Total number of participating patients	900	140

For the patient reported outcomes using questionnaires, all Dutch-speaking patients in the Flemish community pharmacies (approximately 35) are approached. It is hypothesized that 2/3 of patients who consent to a medication review also agree to complete the questionnaires. Considering a drop-out rate of 50%, data should be available for 140 patients (Table 5). In this subset, the score on the Living with Medicines Questionnaire is the main outcome. However, since this instrument has not yet been used in an older polymedicated population, no sample size calculation can be performed.

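### The sample size shows no allowance for clustering by pharmacy, and the analysis text names only within-patient pairing while planning to explore pharmacy-level factors

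*Protocol article*

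**What the plan says.** The Sample size section of the Protocol article sets the structure: "The study aims to approach 75 pharmacies in Belgium" and "Each pharmacy in turn includes 12 patients", which gives 900. The questionnaire subset is 35 pharmacies with 4 patients each, 140 in all.

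The calculation is for adherence. It supposes that pharmacists can "improve adherence using a medication review in half of the patients with a low adherence (10% of all older patients"), and concludes: "a significance level of 5% and power of 80%, a sample size of 746 patients is calculated". The remaining 154 patients (17%) cover drop-out and missing data, and so "a sample size of 900 participants is proposed". The section mentions no ICC, design effect or cluster term.

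On adherence, the Data analysis section says: "The impact will be measured by comparing data before and after the intervention using appropriate statistical tests for paired data". The questionnaires are handled in the same way. A final analysis looks for variables that affect the number of DRPs: "Both patient related factors, process factors and pharmacy related factors will be explored". The software is SPSS, with a per-protocol set and listwise deletion. No model is named, and pharmacy appears only as a source of explanatory factors.

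The Intervention, Outcomes and Data collection sections show that pharmacy staff perform the review and also register the DRPs and interventions that form the main outcome.

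**The concern.** A DRP count depends partly on the patient and partly on how thoroughly a given pharmacist looks and classifies. The article itself shows that practice varies. In the Feasibility study section the pharmacists differed in how they dealt with the physician, and GP involvement remains optional in the main study. Positive correlation within pharmacy is therefore plausible for DRP counts, and possible for the effect of the review on adherence.

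A paired test accounts for the correlation between a patient's own two measurements. It does not account for correlation between patients of the same pharmacy. A factor that is constant within a pharmacy has at most 75 independent values, however many of the 900 patient rows enter the analysis. If those rows are treated as independent, standard errors are too small and chance differences between pharmacies can appear as significant predictors. The study is meant to support implementation of medication review in Belgium, so spurious pharmacy-level predictors would matter.

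**Working it through.** **Inputs from the article.** 75 pharmacies; 12 patients each; two-sided 5% level (sidedness is not stated, so this is assumed); 80% power; low adherence falling from 10% to 5% (half of the 10% improve); 746 evaluable patients. **Assumed input.** The article gives no ICC, so a range of 0.01 to 0.20 is used.

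**1. The plan's own figures.** The drop-out step reproduces: 746 / (1 − 0.17) = 899, and 154 / 900 = 17.1%. The 746 does not. With b the proportion improving, c the proportion worsening, p = b + c and d = b − c = 0.05, the McNemar sample size is

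N = (1.96·√p + 0.842·√(p − d²))² / d².

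- No worsening (p = 0.05): N = 155.
- Before and after states independent (p = 0.14): N = 437.
- Maximum discordance (b = 0.10, c = 0.05, p = 0.15): N = 469.

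A two-sided McNemar N of 746 would need p of about 0.238. That is impossible with margins of 10% and 5%, where p cannot exceed 0.15. Two independent groups give 870 in total (two-sided), or 764 (one-sided with continuity correction), but neither is the paired single-group design. A one-sided McNemar with 5% improving and 2.5% worsening gives 740, but the article states neither that worsening rate nor a one-sided test.

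**2. Effect of ignoring pharmacy, m = 12.** Design effect DE = 1 + (m − 1)·ICC. Standard errors are too small by a factor of √DE. The type I error of a nominal 5% test on a purely pharmacy-level factor is 2·(1 − Φ(1.96/√DE)).

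| Assumed ICC | DE | √DE | Type I error |
|---|---|---|---|
| 0.01 | 1.11 | 1.05 | 6.3% |
| 0.05 | 1.55 | 1.24 | 11.5% |
| 0.10 | 2.10 | 1.45 | 17.6% |
| 0.20 | 3.20 | 1.79 | 27.3% |

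A simulation of 4,000 trials with 75 × 12 patients gave 11.8%, 17.7% and 27.7% at ICC 0.05, 0.10 and 0.20. An analysis of pharmacy means stayed at about 5%.

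**3. Power for adherence at N = 746.** Evaluable patients per pharmacy: 746 / 75 = 9.95. DE = 1 + 8.95·ICC, which is 1.447 at ICC 0.05 and 1.895 at 0.10. The effective N is 746 / 1.447 = 515 and 746 / 1.895 = 394. Power = Φ((d·√N − 1.96·√p) / √(p − d²)).

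- Maximum discordance (p = 0.15): Φ((1.366 − 0.759)/0.384) = 94% with no clustering; 84% at ICC 0.05; 73% at ICC 0.10.
- No worsening (p = 0.05): 99.9% at ICC 0.05, 99.4% at 0.10 and 96% at 0.20.

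At maximum discordance, power stays at 80% or more up to DE = 746 / 468.6 = 1.59, an ICC of 0.59 / 8.95 = 0.066. With no worsening the limit is DE = 746 / 154.6 = 4.83, an ICC of 3.83 / 8.95 = 0.43.

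The ICC in this step is that of the before-after change. Stable differences between pharmacies cancel within each patient, so it may be smaller than the ICC of DRP counts in step 2.

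**The case against.** The strongest reply is that the article nowhere declares patients independent. It asks for suitable paired tests and an exploration of factors, names no model, and uses software that can fit mixed models and GEE. The choice of model is commonly left to a full protocol or analysis plan, and neither is shown. This stands against the reading that the tests are planned as if patients were independent; a reader might infer that, but the text does not say it. It does not remove the point. The sample-size paragraph lists its inputs and accounts for the whole margin above 746 without clustering. The analysis text names one kind of dependence and then commits to pharmacy-level factors. Ordinary paired tests and an analysis by patient row would follow that text and ignore pharmacy.

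Three other stronger readings also fail.

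- A reader might conclude that power falls from 80% to 64% or 53% (DE 1.447 or 1.895). That requires 746 to give exactly 80% for independent patients under the planned test. The 746 cannot be rebuilt, and it exceeds every paired requirement found for a change from 10% to 5% (155 to 469). Nor can the reverse be shown, that 746 was chosen to leave room for clustering.
- A reader might say that the confidence intervals for the main outcome are too narrow. The DRP outcome is descriptive, and the article plans no interval or test for it.
- A reader might extend the inflated type I error to the whole risk-factor analysis. The figures apply to factors constant within a pharmacy, whereas the stated aim is chiefly to identify high-risk patients.

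**Conclusion.** The concern holds in a limited form. Clustering is built into the design, the stated sample-size inputs contain no allowance for it, and the analysis text addresses only pairing within patients.

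The consequence is conditional on two things: an analysis that ignores pharmacy, and a positive ICC. Under both, the clearest damage is to pharmacy-level factors, where the type I error of a nominal 5% test is about 6% at an assumed ICC of 0.01 and 27% at 0.20. Any interval reported for mean DRP counts would have a standard error too small by a factor of 1.05 to 1.79 over the same range.

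For adherence, a shortfall in power is possible but not established. It needs discordance near its maximum together with an ICC of the change above about 0.07. Power is higher if few patients worsen.

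**What to change.** In the Data analysis section, specify how pharmacy is handled in the DRP risk-factor analysis and in the before-after comparisons of adherence and questionnaire scores. The options are a random intercept for pharmacy (with a count model for DRPs), GEE clustered on pharmacy, or cluster-robust standard errors. Wherever an interval is given for a mean DRP count, make it cluster-robust. Confirm that a pharmacy code is kept in the study database; the article describes coded patient data and a pharmacist login but does not say so.

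In the Sample size section, state an assumed ICC range with its design effect, and restate the power at 746 evaluable patients for a named paired test with its discordance assumption.

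The cost is wording and a recalculation. Enrolment does not change. Intervals will be wider, and the stated power may be less favourable than the present text implies.
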